**Methods:**

Four hundred plus children from 4+ schools will either complete the Flavour School programme (experimental group) or have no intervention with normal school teaching (control group), cluster-randomised within-schools, by school class. Baseline data collection will consist of video recorded behavioural observation during a tasting activity, and post-intervention data collection will repeat this activity after the experimental group have completed the intervention. Process measures will be assessed using a teacher engagement feedback questionnaire.

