### Eligibility criteria {10}

#### School inclusion/exclusion criteria

Participation is open to primary schools in London and Leeds regions, for children in reception, year 1 and year 2 (age range 4–7 years). Schools decide which of these year groups will participate in the study. Special needs schools, independent schools and very small schools (less than one class group per year group) will not be included.

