#### Independent measures

Control/intervention groupDate of birth of childSex of childPupil Premium eligibility of childSchoolSchool class

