### Participant timeline {13}

The trial runs over the 2021–2022 school year. Schools nominate eligible year groups for participation. Cluster randomisation will be at the level of paired teaching class groups, within-school. For example, a school chooses year 1 to participate. Year 1 contains two classes, 1A and 1B. At random, class 1A is assigned to the control group and 1B to the experimental group. See Fig. 1. Schools can choose the timing of intervention delivery separately for each pair of classes. Therefore, different class pairs can have different intervention timings.

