#### Plans for assessment and collection of outcomes {18a}

Behavioural data collection is conducted through a tasting activity we call ‘Flavour Explorers’. The activity itself is individual, but is performed in a peer-group of three or four to enable conversation and make the scenario comfortable for the children participating. The children are supervised by the researcher(s). The children sit on cushions on the floor, around a small circular table.

Each child is provided a small tray with nine compartments, each containing one food sample. Each compartment/food sample is marked with a different colour dot sticker. Each child is also provided a ‘My Tasting Card’, with nine colour blobs matching the food samples/compartments. When a child tries a food, they use ‘emoji’ style drawings to note their liking for the food (sad face, neutral face, or happy face) on their Card. See Fig. 2. Children are given as much time as they need (within reason), and sessions typically last between 8 and 12 min.

The sample consist of seven vegetables (including a legume and a herb), and two fruits, and include both common/familiar and obscure/unfamiliar produce. Different food sample sets will be used for pre- and post-intervention testing, counterbalanced at random by school class group. See Additional file 1: Appendix 1 for more details.

Flavour Explorers sessions will be video recorded, with an individual video stream for each child. A dedicated Yi4k+ action camera for each child is located in the centre of the table. The My Tasting Cards provide the raw data for analysis of willingness-to-taste (WTT) and liking, whilst video/audio provides raw data for affect from facial expression, and verbal engagement (Fig. 3).

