### Statistical methods

#### Statistical methods for primary and secondary outcomes {20a}

For each participant, pre/post-intervention difference will be calculated for each primary measure, plus the normalised sum of primary measures (to represent overall ‘curiosity and confidence’). Each set of data will be analysed using regression models with pre-post difference as the outcome. Secondary measures will be examined using the same methods as primary measures. The number of clusters is too small to analyse using a multi-level model, however school and class will be included as a covariate.

For each participant, data will be collected at baseline and follow-up. The main outcomes (dependent variables) will be individual scores in WTT, enjoyment/engagement (from facial expression), and verbal engagement at follow-up. The difference in scores between the intervention and the control group will be calculated for each of the primary measures, plus an overall score consisting of the sum of primary measures which represents overall curiosity and confidence. Each set of data will be analysed using two level regression models (where appropriate), to take into account the clustering of children within schools. The analysis will be adjusted for baseline scores.

The intervention should benefit those children most in need of support. To reflect this in our analysis, we will split the participants into three sub-groups according to their score on a given measure at baseline (low, mid, high). Each grouping will cover 1/3 of the range for that measure. It is important that any benefits be observed in the low and/or mid groups and not just be driven primarily by the high group. High scores are considered desirable in all measures.

The liking secondary measure will be examined using the same regression methods.

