#### Methods for additional analyses (e.g. subgroup analyses) {20b}

At the individual level, we will control for any effects of sex, age, and Pupil Premium^2^ eligibility. At the group level, we will control for any effects of school and school class group. Any group differences will be interpreted in the light of information about process adherence and teacher engagement, as reflected in the teacher survey (see Additional file 1: Appendix 3).

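### Food-set order is drawn by class, the unit also randomised to arm, so chance imbalance between arms in the follow-up set adds avoidable noise to the treatment contrast

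*Protocol article*

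**What the plan says.** Under Plans for assessment and collection of outcomes {18a}, the protocol article states: "Different food sample sets will be used for pre- and post-intervention testing, counterbalanced at random by school class group". It refers to Appendix 1 of the additional file for more detail; that file is not shown.

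Under Participant timeline {13}: "Cluster randomisation will be at the level of paired teaching class groups, within-school". The worked example sends the two classes of a pair to opposite arms: "At random, class 1A is assigned to the control group and 1B to the experimental group". The term class group means a single class, as the school eligibility wording shows: "very small schools (less than one class group per year group) will not be included".

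The number of classes is not given. The abstract plans for "Four hundred plus children from 4+ schools", and Statistical methods {20a} says: "The number of clusters is too small to analyse using a multi-level model, however school and class will be included as a covariate".

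Food set does not appear among the Independent measures, which are arm, date of birth, sex, Pupil Premium eligibility, school and class. Section {20b} begins "At the individual level, we will control for any effects of sex, age", goes on to Pupil Premium eligibility, and at group level names only school and class. Section {20a} adds baseline score.

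**The concern.** Two class-level assignments, arm and set order, are made on the same small number of classes, and nothing in the text shown ties one to the other. When the two classes of a pair have opposite orders, the intervention and control children in that pair are tested on different foods at both visits. If one set is easier to taste, or provokes more expression, that pair's arm comparison carries the set difference as well as any intervention effect.

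The terms named in the plan do not remove this:

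- School does not capture it, because order can differ between two classes of one school.
- Class as a fixed effect cannot separate it, because arm and order are both constant within a class.
- Baseline score makes it larger, because each class had the other set at baseline.

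What is at stake is precision, and the reading of the one allocation that is actually drawn. The pairing was meant to give a like-for-like comparison, and it is weakened by a nuisance that the design could remove.

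**Working it through.** **The plan's own figure.** Sample size {14} gives 160 per arm for a difference of 0.5 foods, SD 1.38 and 90% power. With a two-sided 5% level (assumed; not stated there), n = 2 × (1.960 + 1.282)² × 1.38² / 0.5² = 160.1, so the figure reproduces. It does not depend on food set. It also comes from a four-food task in children aged 1 to 3, so the nine-food shifts below are not compared with its 0.5 target.

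**Number of pairs (assumption).** At 20 to 30 consented children per class, 400 children is 400/30 = 13.3 to 400/20 = 20 classes, or about 7 to 10 pairs.

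**Imbalance.** Assume two sets. Let K be the number of pairs and D the share of intervention classes with a given set at follow-up, minus the same share among control classes. If each class draws independently with probability 1/2, SD(D) = √(2 × 0.25 / K). At K = 8 this is √0.0625 = 0.25. Exact enumeration of two Binomial(K, 1/2) counts gives:

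| Pairs | SD(D) | P(abs D ≥ 0.25) | P(abs D ≥ 0.5) | P(D = 0) |
|---|---|---|---|---|
| 7 | 0.267 | 42.4% | 5.7% | 20.9% |
| 8 | 0.250 | 45.4% | 7.7% | 19.6% |
| 9 | 0.236 | 23.8% | 3.1% | 18.5% |
| 10 | 0.224 | 26.3% | 4.1% | 17.6% |

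The 25-point column jumps because counts are whole numbers: a difference of two classes suffices at 7 or 8 pairs, and three are needed at 9 or 10. The SD falls smoothly and is the steadier summary.

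**Other readings of the assignment rule, at 8 pairs.** If exactly half of all classes get each order, without regard to arm, P(abs D ≥ 0.5) is 13.2%. If orders are opposed within every pair, with a coin toss per pair, it is 28.9%. If order is matched within pairs, or balanced within each arm, D = 0 on class counts.

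**Complete confounding (abs D = 1).** At 7 pairs this is 0.01% under independent draws and 1.6% under opposed orders. At 8 pairs it is about 0.003% and 0.8%.

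**Shift in the arm contrast.** Let s be the difference between sets in mean foods tasted, out of nine. The arms differ by sD at follow-up and by −sD at baseline, because the sets swap.

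- Follow-up score alone: sD
- Adjusted for baseline with slope b: sD − b(−sD) = sD(1 + b)
- Pre-post difference: sD − (−sD) = 2sD

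The documents do not give s or b. For D = 0.25:

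| s (foods of nine, assumed) | Follow-up | Adjusted, b = 0.5 (assumed) | Pre-post difference |
|---|---|---|---|
| 0.25 | 0.06 | 0.09 | 0.125 |
| 0.5 | 0.125 | 0.19 | 0.25 |
| 1 | 0.25 | 0.375 | 0.50 |

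Since SD(D) = 0.25 at 8 pairs, the same entries are the SDs of the added noise at that size.

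**The case against.** Counterbalancing usually implies some enforced balance, and Appendix 1 may describe a scheme that is already balanced within arm or matched within pair. A journal article may leave such detail to a supplement, and model terms to an analysis plan. This stands as a reason for caution. But the main text does state the rule, by class and at random, without mentioning arm or pair, and followed as written it permits the imbalance.

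A reader might infer that food set biases the trial, or could be fully confounded with treatment. The documents do not support that. If the set draw is independent of arm, the estimate is unbiased over repeated randomisations; what remains is extra class-level variance and a conditional shift in the single trial that is run. Complete confounding is remote at the likely number of pairs.

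The set difference may also be small. Both sets share a broad composition (seven vegetables and two fruits, familiar and unfamiliar), and about 77% of pilot children tasted 7 to 9 items, which leaves limited room for a mean shift of a whole food. That is why a range down to 0.25 foods is shown. The pilot figure concerns counts tasted, however. The protocol itself says that sour or disliked foods provoke strong negative expressions, so the facial measures could also respond to the set.

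Finally, a reader might take the doubling as general. It applies only to the pre-post version in the first paragraph of {20a}. The Outcomes section and the second paragraph of {20a} specify follow-up scores adjusted for baseline, where the factor is 1 + b.

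**Conclusion.** The concern holds as one of avoidable noise. Set order is assigned at random at the level that is also randomised to arm, and nothing shown matches it within pairs, balances it by arm or adjusts for it. Under independent draws, an imbalance of at least 25 points has a chance of about 24% to 45% for 8 to 10 pairs, and exact balance a chance of about 18% to 20%. For a set difference of 0.25 to 1 food of nine, an imbalance of 25 points moves the contrast by 0.06 to 0.25 foods on follow-up scores, and by up to twice that on pre-post differences.

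These sizes rest on assumptions: the number of pairs, independent draws, two sets, and the size of the set difference. If Appendix 1 already matches order within pairs or balances it by arm, the point reduces to stating so in the main text.

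**What to change.** Give both classes of a randomised pair the same set order, and alternate or randomise the order across pairs. The within-pair comparison is then always on the same foods and D = 0 on class counts, whatever the number of pairs. State this rule in {18a}. It costs a change to the order list, with no additional foods, sessions, staff or children. Because order still varies across pairs, the food set alone does not reveal the time point to the video coders.

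For pairs already tested on different orders, include follow-up food set as a covariate in a model that has pair or school terms but no fixed class effects; with fixed class effects the set term is aliased. The covariate uses one class-level degree of freedom. With pair terms it can be estimated unless every pair is discordant in the same direction.

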**Fig. 3 Fig3:**
[figure not shown]
Timeline of the ‘Flavour Explorers’ data collection activity

#### Plans to promote participant retention and complete follow-up {18b}

Participants who leave the school/class during the trial will not be included in the trial. The intervention is enjoyable and is integrated into school-time teaching. No follow-up measures are currently planned, due to shortening of the trial to accommodate COVID-19-related time pressures.

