### Outcomes {12}

The observational scenario is a tasting activity done in small groups (see the “Plans for assessment and collection of outcomes {18a}” section). The test activity will conducted < 6 weeks before (baseline) and < 6 weeks after intervention delivery is completed. Analysis metric for all measures is follow-up scores, adjusted for baseline, for all children.

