**Fig. 1 Fig1:**
[figure not shown]
Participant timeline and cluster randomisation

Teachers will be instructed to ensure Flavour School delivery respects class delineations, to minimise contagion. The control group receives no intervention (i.e. the standard curriculum). Pre- and post- intervention data collection is conducted for both the experimental and control groups. The control group can receive the intervention after post-intervention data collection is complete, at the school’s discretion.

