### Sample size {14}

There is no perfectly comparable study upon which to base our sample size estimates, as our behavioural measures and study design are novel to the domain. Using a similar testing method in a younger age group (1–3 year olds), Dazeley and Houston-Price [31] reported that out of 4 foods (2 fruits, 2 vegetables) offered to nursery school children, the mean number of foods tried was 1.44 with a standard deviation of 1.38. To measure mean increases of 0.5 (the equivalent of 50% of children eating one more food), using the same standard deviation found by Dazeley and Houston Price, a sample size of 160 children is needed in each arm (control and intervention) to provide 90% power. We will aim to recruit 400+ children, but recruitment may be challenging due to ongoing pandemic COVID-19 conditions.

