#### Methods in analysis to handle protocol non-adherence and any statistical methods to handle missing data {20c}

Analysis will follow intention-to-treat principles for all participants who complete the intervention. Adherence will be assessed via a teacher survey and supported via personal contact with participating teachers and school visits by researchers to observe delivery of the intervention and offer support/guidance where necessary. A participant’s data will be excluded if it is not possible to gather post-intervention data.

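### The leaver rule drops a child who changes class but stays in the school and can still be tested, which conflicts with the intention-to-treat principle the protocol claims

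*Protocol article*

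**What the plan says.** Four parts of the protocol article bear on which children are analysed.

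- Retention and follow-up {18b}: "Participants who leave the school/class during the trial will not be included in the trial". The slash makes leaving the class a sufficient reason for removal, separate from leaving the school.
- Non-adherence and missing data {20c}: "Analysis will follow intention-to-treat principles for all participants who complete the intervention", and then "A participant’s data will be excluded if it is not possible to gather post-intervention data".
- Participant timeline {13}: "Cluster randomisation will be at the level of paired teaching class groups, within-school". The section's own example splits classes 1A and 1B of one year group. The text after Fig. 1 adds: "Pre- and post- intervention data collection is conducted for both the experimental and control groups".
- Outcomes {12}: "Analysis metric for all measures is follow-up scores, adjusted for baseline, for all children".

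Nowhere does the article say that a child who changes class is kept, tested, or analysed in the original class.

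**The concern.** A move between the two classes of a pair is a crossover between arms. Intention-to-treat analysis exists to handle that case: the child stays in the arm held at allocation and is measured if possible. The leaver rule removes the child instead. Because the exclusion depends on something that happens after allocation, the retained children in the two arms need no longer be comparable, and crossover disappears from the report.

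This is not detail that an article would leave to an analysis plan. It is a positive exclusion rule, and it discards a baseline and an obtainable follow-up. The blinding section {17a} says that children and teachers know the allocation, so moves that depend on arm cannot be ruled out.

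**Working it through.** **1. One child, each rule in turn.** Take a child in class 1A at allocation who moves to 1B before the follow-up session.

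- Leaver rule {18b}: has left the class, so is removed.
- Missing-data sentence {20c}: the partner class is tested in the same school, so follow-up can normally be gathered and this sentence does not remove the child.
- Completer restriction {20c}: if 1A was the intervention class and the move came before delivery ended, the child would generally be removed here too. If 1A was the control class, there was no intervention to complete. If the move came after delivery ended and before the post-test (a window of under 6 weeks, Outcomes {12}), the intervention was completed.

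So the leaver rule has an effect of its own at least for control-class movers and for children who move between the end of delivery and testing. If the completer restriction were deleted, it would still remove every class-changer.

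**2. Number affected.** The protocol gives no rate of class change, so 2-5% is an assumption. With the recruitment aim of 400 (Sample size {14}):

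- 0.02 x 400 = 8 children
- 0.05 x 400 = 20 children

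**3. Power.** First the plan's own figure: difference 0.5, SD 1.38, 90% power. Two-sided alpha of 0.05 and equal arms are assumed here, as the section states neither.

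n per arm = 2 x (1.960 + 1.282)^2 x 1.38^2 / 0.5^2 = 160.1, or 161 rounded up, against the stated 160. Power at 160 per arm is 90.0%, so the figure is reproduced.

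Power after excluding 2% or 5%, by the same individual-level formula with no allowance for clustering:

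| Per arm | No loss | 2% lost | 5% lost |
|---|---|---|---|
| 160 | 90.0% | 89.4% | 88.5% |
| 200 | 95.2% | 94.8% | 94.2% |

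The loss of power is minor.

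**4. Bias.** Let d be the share of an arm excluded and g the amount by which the excluded children's baseline-adjusted follow-up falls below that of the children retained. The retained mean then exceeds the full-arm mean by d x g, and the arm contrast shifts by

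d(intervention) x g(intervention) - d(control) x g(control).

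- Equal shares and equal g in both arms: the shift is zero.
- Purely for illustration, 4% excluded in one arm and none in the other, with a gap of 1-3 foods out of nine remaining after baseline adjustment: 0.04 x 1 = 0.04 to 0.04 x 3 = 0.12 of a food.

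Every input to the second case is assumed. Baseline adjustment would absorb much of a gap that already existed at baseline, so a remaining gap of 1-3 foods is a severe case.

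**The case against.** Several stronger readings are tempting, and the protocol does not support them.

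- A reader might infer that {18b} and {20c} flatly contradict each other. They do not: {20c} gives one reason for exclusion and does not say that it is the only one, so both rules can operate together. The conflict is with the intention-to-treat principle.
- A reader might take the closing words of "Analysis metric for all measures is follow-up scores, adjusted for baseline, for all children" as a promise to analyse everyone. That sentence defines the metric, and the individual inclusion criteria already limit the data to children with caregiver consent.
- A reader might suppose that movers are mainly cautious eaters or children with extra needs, moved by caregivers who know the allocation. The protocol says nothing about who changes class. Section {17a} names children and teachers as unblinded, not caregivers.
- A reader might express the illustrative shift as a share of the 0.5-food target. That target and its SD come from a test of four foods in children aged 1-3 years, whereas this trial offers nine, so the ratio would mix scales. It would also treat a raw gap as bias, although the analysis adjusts for baseline.

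The strongest objection is overlap. The completer restriction in {20c} is the larger departure from intention-to-treat and would generally catch intervention-class children who move during delivery. One correction can repair both. This argues for making the changes together. It does not make the leaver rule harmless, because control-class movers and late movers are caught by that rule alone.

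The practical objection also stands in part. Food sets are counterbalanced by class (Plans for assessment {18a}), so a mover tested with the new class might meet the baseline set again. Class pairs may also run on different timings (Participant timeline {13}), so a move outside the pair could miss a suitable session.

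**Conclusion.** The point holds in limited form. As written, {18b} excludes children who remain in the school and can be tested, because of an event after allocation. That is inconsistent with the intention-to-treat principle claimed in {20c}, and nothing else in the article repairs it.

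The size is unknown and probably small, since delivery lasts one school term. The figure of 8-20 children rests wholly on the assumed 2-5% rate. Loss of power is minor at those rates. Bias needs exclusions that differ between arms, in number or in kind, and movers who differ in baseline-adjusted follow-up. The protocol shows neither, but the present rule would also hide both if they occurred. The change is worth making because it is cheap and removes an avoidable exclusion. The evidence does not support calling it a major threat to the result.

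**What to change.** Reword {18b} and align {20c} with it so that one rule defines the analysis set:

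- Only children whose post-intervention data cannot be gathered, for example school-leavers, count as lost to follow-up.
- Children who change class within the school are tested where a session is feasible, using the follow-up food set assigned to their original class.
- They are analysed in the class and arm held at allocation, and the move is recorded.
- Class moves and losses to follow-up are reported by arm.
- The restriction in {20c} to those completing the intervention is revised at the same time. Otherwise it would still exclude some of these children.

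The cost is a short change in two sections, some logistics in supplying the right food set and finding a session, and slight dilution of the contrast from the few who cross over. That dilution is the normal price of analysing as allocated.
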